## Abstract

**Background:**

Chagas' disease is the major cause of disability secondary to tropical diseases in young adults from Latin America, and around 20 million people are currently infected by *T. cruzi*. Heart failure due to Chagas cardiomyopathy is the main clinical presenation in Colombia. Heart failure due to Chagas' disease may respond to digoxin, diuretics and vasodilator therapy. Beta-adrenoreceptor antagonism seems to protect against the increased risk of cardiac arrhythmia and sudden death due to chronic sympathetic stimulation. The aim of this study is to evaluate the effects of the selective beta-adrenergic receptor blocker Bisoprolol on cardiovascular mortality, hospital readmission due to progressive heart failure and functional status in patients with heart failure secondary to Chagas' cardiomyopathy.

**Methods/design:**

A cohort of 500 *T. cruzi *seropositive patients (250 per arm) will be selected from several institutions in Colombia. During the pretreatment period an initial evaluation visit will be scheduled in which participants will sign consent forms and baseline measurements and tests will be conducted including blood pressure measurements, twelve-lead ECG and left ventricular ejection fraction assessment by 2D echocardiography. Quality of life questionnaire will be performed two weeks apart during baseline examination using the "Minnesota living with heart failure" questionnaire. A minimum of two 6 minutes corridor walk test once a week over a two-week period will be performed to measure functional class. During the treatment period patients will be randomly assigned to receive Bisoprolol or placebo, initially taking a total daily dose of 2.5 mgrs qd. The dose will be increased every two weeks to 5, 7.5 and 10 mgrs qd (maximum maintenance dose). Follow-up assessment will include clinical check-up, and blood collection for future measurements of inflammatory reactants and markers. Quality of life measurements will be obtained at six months. This study will allow us to explore the effect of beta-blockers in chagas' cardiomyopathy.

## Background

Chagas' disease (CD) is a permanent threat for almost a quarter of the population of Latin America. Although the disease has been described in almost all Central and South America, clinical presentation and epidemiological characteristics are variable among the different endemic zones [1,2]. A wide range of prevalence rates has also been reported suggesting local differences in transmission of the disease as well as differences in vectors and reservoirs [3].

Chagas' cardiomyopathy (CCM) represents a serious public health problem in most Latin American countries, and the most recent statistics provided by the World Health Organization indicate that 100 million persons are exposed to the disease and approximately 20 million are currently infected [4]. Interestingly, in addition to the natural infection foci, an increase in the transmission associated with blood transfusions has also been noticed. These statistics are considered an underestimation of the real rates of infection, most likely due to lack of reports from highly endemic retired rural communities. In countries in which the disease is endemic such as Colombia, Venezuela and Brazil, the overall prevalence of infection averages 10%. However, in highly endemic rural areas rates have ranged from 25% to 75% [5]. Prevalence of infection varies widely even between cities and provinces within the same country because of variations in climate, housing condition, public health measures, and urbanization. The actual prevalence of clinical Chagas' disease and the number of case fatalities are largely unknown, mainly because case reporting is virtually nonexistent in many areas in which CD is highly endemic.

Congestive heart failure (CHF) is a late manifestation of CD that results from structural abnormalities and extensive and irreversible damage to the myocardium. Heart failure in *T. cruzi *infected patients usually occurs after age 40 and follows AV block or ventricular aneurysm. However, when CHF develops in patients less than 30 years old it is frequently associated with a more aggressive myocarditis and an extremely poor prognosis [1]. The mortality attributable to CD is related to the severity of the underlying heart disease. Very high mortality is often found in patients with CHF [2], however, mortality in asymptomatic seropositive patients varies greatly between geographic regions, suggesting that other factors may influence the severity and progression rate of cardiac disease. It is believed that cardiac damage in CD progresses slowly but steadily over decades, from subclinical myocarditis to mild segmental abnormalities with conduction defects, to severe ventricular structural abnormalities, and finally to overt congestive heart failure and sudden cardiac death. Besides the poor prognosis of CHF due to Chagas' disease, it is important to estimate the risk of complications and death in patient infected with *T. cruzi*. Unfortunately, few clinical studies have addressed this issue. Most *T. cruzi *infected patients have mild or no clinical disease, however, the percentage of infected people that will develop detectable cardiac abnormalities is approximately 30 to 40% [3], but only 20% of them will develop symptomatic cardiac involvement [6]. Like CHF from other causes, CHF due to CD responds to digital, diuretics and vasodilators therapy [7]. Additionally, some studies have shown that angiotensin-converting enzyme (ACE) inhibitors improve survival in patients with moderate to severe CHF due to CD [8]. In spite of its benefits on patients with non Chagas' disease CHF, there is considerable uncertainty about the potential role of ACE inhibitors in patients with CHF due to Chagas' disease. *Captopril*, and ACE inhibitors, has been shown to reduce neurohormonal activation and non-lethal arrhymias in a small number of patients with Chagas' heart failure [8,9].

Another intervention currently included in the management of CHF patients is the use of b blockers. Observational studies [10] as well as clinical trials [11,12] have shown that b-blockers reduce morbidity and mortality in CHF patients. The effects of b-blockers on CHF patients are being studied in large scale clinical trials [13-19]. Apparently, the cardiac sympathetic hyperstimulation that initially helps to preserve ventricular function in CHF patients, later on, results in an increased risk of cardiac arrhythmia and sudden death [20] b-adrenoreceptor antagonism seems to protect against the deleterious effects of chronic sympathetic stimulation [21]. Moreover, b-blockers reduce heart rate, improve myocardial energetic balance and lead to a less negative force-frequency relationship. These effects contribute to the benefits of b-blocker therapy in CHF patients.

Clinical studies with Carvedilol, an alpha-1 and non selective b-blocker, further support the beneficial effects of b-adrenoceptor antagonism [18,19,23,24]. Results from the US CARVEDILOL and COPERNICUS trial, suggest that prognosis in CHF may partly depend on left ventricular dysfunction improvement as well as sympathetic activity reduction [18,23]. However, additional data are needed to define more precisely the relationships between heart rate reduction, left ventricular function improvement and survival in CHF patients. In some studies like CIBIS II and MERIT HF, the beneficial effects of the selective b- blockers on morbidity and mortality were observed specially in patients functional class II and III. In COPERNICUS a multicentric placebo controlled clinical trial with *Carvedilol*, these effect was ascertained even in patients functional class IV [23], demonstrating that patients with CHF, independently of their functional class, should receive b-blocker therapy.

Current guidelines for the management of CHF strongly recommend the use of beta-blockade in management of CHF. However, these benefits have not been proven in Chagas' cardiomyopathy [25,26]. Nevertheless, there are reasons to believe that beta-blockade will be beneficial for these patients.

First, patients with CHF due to CD have a raised end-diastolic pressure associated with a low systemic blood pressure, which lead to low transmyocardial pressure gradient and subendocardial ischemia. Therefore, reduction in myocardial oxygen demand due to beta-blockade could be expected to be beneficial in this situation, even in non ischemic CHF patients. Second the reduction in sudden cardiac deaths and serious ventricular arrhythmias suggest that an anti arrhythmic effect is an important component of beta-blockade. This anti-arrhythmic effect is explicable not only on an anti-ischemic basis but also by blockade of sympathetic activity, which is indeed increased in patients with Chagas' cardiomyopathy. Third, prolonged activation of the sympathetic nervous system can accelerate the progression of heart failure, and the rate of progression can be substantially decreased using pharmacological agents that interfere with sympathetic activity in the heart and peripheral blood vessels. There is clear evidence of increased circulating beta-adrenergic antibodies in Chagas' disease providing further theoretical support for the use of beta-adrenergic blockade in this group of patients.

Beta-blockers already proven to be beneficial in CHF patients are metoprolol, bisoprolol and carvedilol, drugs which have been tested in over 10.000 patients in more than 20 placebo-controlled clinical trials enrolling men and women with systolic dysfunction due to ischemia, hypertension and dilated idiopathic cardiomyopathy. Bisoprolol is a beta-1 selective blocker with the highest selectivity for this receptor, in doses less than 10 mg it has very little or no effect on beta-2 receptors. Bisoprolol was first tested in CHF in the CIBIS I trial which enrolled 641 patients and showed improvement in functional class, less hospitalizations for heart failure and a trend to improved survival. The much larger randomized CIBIS II assigned 2647 patients with class III or IV HF and an LVEF <40 percent to bisoprolol or placebo; the patients also received standard therapy with diuretics and ACE inhibitors. After an average follow-up of 1.4 years, the trial was prematurely stopped when the benefits were observed in the active treatment group: significant reduction in total all-cause mortality (11.8 versus 17.3 percent] that was independent of the severity or cause of HF. This benefit was primarily due to a reduction in SCD (3.6 versus 6.3 percent, p < 0.001], with a non-significant trend toward fewer deaths from HF; significant 15 percent reduction in hospital admissions for any cause and a 30 percent reduction in admissions for HF (p < 0.0001). Considering all the beneficial effects beta-blockers in patients with mild to severe CHF due to ischemic and non ischemic disease, there is no data regarding its potential effects in patients with CHF due to Chagas' disease. Based on the aforementioned we propose to develop a multi-center placebo controlled clinical trial to evaluate the effect of *Bisoprolol *in patients with CHF due to CD.

### Consquences of Chagas' disease

CD is the major cause of disability secondary to tropical diseases in young adults from Latin America. In Colombia, 18% of the population lives in CD endemic areas, 900,000 people are infected and over three million are at high risk of being infected. The Northeastern region carries the highest *T. cruzi *infection rate and CD prevalence. However, the incidence of CCM among *T. cruzi *infected people is unknown and the mechanisms that lead from infection to CCM are uncertain. The mechanisms that trigger the development of CCM in 20%–30% of those infected remain a matter of debate.

Despite the high social burden of the disease no large clinical trials have been performed to determine the effects of standard heart failure therapy on hard outcomes in patients with CCM. Experimental and clinical evidence supports the fact that CCM may be primarily an adrenergic cardiomyopathy. Circulating antibodies to beta-adrenergic receptors have recently been described by Esterin-Borda et al providing further support to the "adrenergic hypothesis". A marked reduction in overall mortality and significant improvement in quality of life, HF hospital admissions, reduction in sudden cardiac death have been reported by the mayor clinical trial using beta-adrenergic blockade. The CIBIS trials using Bisoprolol have definitely established the beneficial effects of this compound in patients with both ischemic and non-ischemic dilated cardiomyopathy and HF. We therefore hypothesize that administration of Bisoprolol compared to placebo in patients with CCC on standard HF therapy (Digoxin, ACEi, Diuretics) will have a 30% RR in a specified predetermined composite outcome.

### Expected impact

We expect that Bisoprolol in patients with CCM will determine a 30% relative risk reduction in mortality and morbidity. In the long term, we expect that this project will contribute to reduce the impact of the CCM and the health burden on the Colombian's health care system, particularly related with HF secondary to CCM.

### Direct and indirect user

The direct users will be the seropositive subjects for *T. cruzi*, with different NYHA functional class of heart failure that will recieve b-blocker therapy, which may reduce the morbidity and mortality in these patients. Other direct users will be all physicians in charge of managing these patients. They may have more accurate information regarding the current managment of Chagas' disease. The indirect user will be the Colombian health policy developers which will be benefited by the results of this study, in order to decrease the economic burden that CCM has on the Colombian health care system.

## Methods

### Objectives

In order to achieve these objectives we defined primary and secondary outcomes which apply to this specific cardiomyopathy, addressing the higher incidence of ventricular arrhythmias and heart block.

### Primary objective

To investigate the effect of the beta-blocker bisoprolol on survival and HF hospitalization rates, and other previously predefined outcomes in patients with Chagas' cardiomyopathy and heart failure.

### Secondary objective

To investigate the effect of the beta-blocker bisoprolol on quality of life, conduction disease progression and need for electrical therapy (i.e. pacemaker, ICD, CRT).

### Hypotheses

1. Bisoprolol will reduce cardiovascular death in patients with Chagas' cardiomyopathy with heart failure functional class NYHA II to IV.

2. Bisoprolol is safe in patients without advanced heart block.

3. Bisoprolol will significantly reduce hospitalization rates due to heart failure in patients with Chagas' cardiomyopathy in functional class NYHA II to IV.

### Study design

CHARITY is a multicenter randomized prospective, double blind, placebo-controlled, forced-titration study in subjects with CHF secondary to CCM.

### Study development

The study will last 2 years. Patient recruitment will take 12 months with an average follow-up time of 1.5 years per patient.

1. Months 0 to 2: Training of the Personal and techniques standardization

2. Months 2 to 6: Patients recruitment and data recollection

3. Months 6 to 24: Follow up of patients

4. Months 24 to 30: Data analysis

Those subjects with positive serology for *T. cruzy *who meet the inclusion/exclusion criteria will receive placebo or Bisoprolol in addition to standard therapy for chronic heart failure which includes an ACE-inhibitor and may include diuretics or other medication such as digitalis or nitrates for heart failure. Patients included in CHARITY should be on stable doses of an ACE-inhibitor. Diuretics can be added to treatment as needed but patients must be on stable doses of each drug during four weeks prior to randomization.

500 subjects will be randomized in two arms; one will receive oral bisoprolol and the other placebo, during the duration of the study. Forced titration will start with the lowest oral dose of 2.5 mg qd and will be up-titrated in 2.5 mg increments every two weeks until the maximum tolerated dose is achieved or 10 mg qd is reached. In case of intolerance, dose will be reduced to the previously tolerated lower dose. Subjects not tolerating the lower dose of 2.5 qd will have a treatment interruption. The best tolerated dose will be continued for one month, then a security visit will re-asses tolerance. Thereafter patients will be controlled every three months until they complete the mean follow-up period of two years. Standard heart failure therapy with ACE-inhibitors, diurectics, digitalis and nitrates will be strongly reinforced in both parallel arms.

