### Follow-up period

ECG tracings will be recorded during the security visit and at 1 and 2 years.

Patients will be followed for two years after randomization.

Repeat echocardiograms will be recorded at 1 and 2 years of follow-up along with HF Quality of-life questionnaire and six-minute walk tests.

Clinical measurements will be obtained every three months along with an assessment of treatment adherence and tolerance. Mortality and hospitalization events will be ascertained by telephonic interview and verified with hospital charts review, up to two years after randomization.

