### Endpoint definitions

1. Cardiovascular death: any death attributable to a cardiac or vascular cause occurring within two years after randomization.

2. Non-cardiovascular death: death from any cause excluding cardiovascular diseases occurring within two years after randomization.

3. Hospital admission/hospitalization caused by heart failure: admission in a hospital or clinic during at least 24 hours caused by heart failure worsening. It excludes procedures and hospitalization for procedures which have been scheduled and not due to worsening of the current heart failure condition since randomization.

4. Heart failure worsening: decline of at least one functional class as defined by the New York Heart Association occurring during any inter- visit period of three months needing inotropic support, IV diuretics, medication dose adjustments or additional drugs for compensation.

5. Perceived quality of life worsening: increase in the "Minnesota living with heart failure" test score of at least 10 points. The test' s score ranges from 0 (best) to 100 (worst).

6. New AV block: appearance of any AV conduction disturbance including first, second and third degree AV block after randomization.

7. Bradycardia requiring pacemaker implantation: ventricular rates < 50 per minute due to any cause including sick-sinus syndrome and AV block, causing symptoms or disability and complying with current indications for permanent pacemaker implantation.

8. ICD: Implantable cardioverter-defibrillator indicated for the prevention and treatment of sudden death, ventricular tachycardia/ventricular fibrillation.

9. CRT: cardiac resynchronization therapy or biventricular pacing or ventricular bifocal pacing for the treatment of advanced heart failure.

10. PM: permanent pacemaker for the treatment of conduction disturbances.

11. Clinically significant ventricular arrhythmias: sustained monomorphic ventricular tachycardia or ventricular fibrillation with symptoms caused by hemodynamic or perfusion alterations, circulatory collapse or syncope.

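### Recruitment length and follow-up are each stated in conflicting ways, and under a month-24 close essentially no patient can reach the two-year assessments

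*Protocol article*

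**What the plan says.** All of this is in the protocol article.

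- **Study development, opening:** "The study will last 2 years. Patient recruitment will take 12 months with an average follow-up time of 1.5 years per patient".
- **Study development, month list:** training in months 0 to 2, then "Months 2 to 6: Patients recruitment and data recollection", follow-up in months 6 to 24, and data analysis in months 24 to 30.
- **Study development, last paragraph:** three-monthly visits go on "until they complete the mean follow-up period of two years".
- **Follow-up period:** "Patients will be followed for two years after randomization". ECGs are due at the security visit and at 1 and 2 years. For the other measures: "Repeat echocardiograms will be recorded at 1 and 2 years of follow-up along with HF Quality of-life questionnaire and six-minute walk tests". Deaths and hospitalizations are ascertained up to two years.
- **Endpoint definitions:** cardiovascular death is "any death attributable to a cardiac or vascular cause occurring within two years after randomization". Non-cardiovascular death has the same window.
- **Interim timing:** Statistical methods places the formal efficacy interim one year after the recruitment phase. The Data and Safety Monitoring Board text places a review of safety, efficacy and progress 12 months after the first randomization.

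**The concern.** Recruitment is given two lengths, 12 months and 4 months. Follow-up is given as an average of 1.5 years, a mean of two years, and two years for each patient. The only closing date in the text is month 24, and recruitment is not listed to start until month 2. A patient randomized at month 2 has 22 months by then, and everyone later has less.

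Three things are at stake:

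- The 2-year ECG, echocardiogram, quality-of-life and walk-test data could not be collected. Worsening of perceived quality of life is a listed secondary outcome.
- Sites and data management cannot tell when a patient's follow-up ends or when the database can be locked.
- The planned exposure, on which the number of events depends, changes with the sentence that is followed.

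**Working it through.** **Inputs.** Close of follow-up: month 24 (month list, and "The study will last 2 years"). Recruitment: months 2–6 (month list) or 12 months (opening sentence). The 12 months may start at month 0, ignoring the training phase, or at month 2, after it. Total 500 patients, 250 per arm (Abstract; Study development).

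**Formulas.** For recruitment from month s to month e and a common close at month C:

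- longest follow-up = C − s
- shortest follow-up = C − e
- mean follow-up under uniform accrual (assumed) = C − (s + e)/2
- close needed for two years in every patient = e + 24

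**The plan's own figure first.** The 1.5-year average is reproduced with s = 0, e = 12, C = 24: 24 − 6 = 18 months. The month list does not give it: 24 − (2 + 6)/2 = 20 months, or 1.67 years. The listed follow-up phase, months 6 to 24, is itself 18 months long. The 1.5 years may therefore be the shortest follow-up labelled as an average; the text does not say.

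| Recruitment | Shortest / mean / longest at month 24 | Who reaches 24 months | Close needed for two years in all | Pace for 500 |
|---|---|---|---|---|
| Months 2–6 | 18 / 20 / 22 | nobody | 6 + 24 = 30 | 500/4 = 125 per month |
| 12 months from month 0 | 12 / 18 / 24 | day-one patients only | 12 + 24 = 36 | 500/12 ≈ 42 per month |
| 12 months from month 2 | 10 / 16 / 22 | nobody | 14 + 24 = 38 | ≈ 42 per month |

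No row has a mean of two years. In the third row, patients randomized in months 12–14 miss the 1-year visit as well. That is 2/12, about one in six. Month 30, the earliest close that gives everyone two years, is when the calendar ends data analysis.

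**Interim timing.** One year after the end of recruitment is month 18, 24 or 26 for the three rows. With 12-month recruitment it falls on the close or after it. Twelve months after the first randomization is month 14, 12 or 14, if the first patient enters when recruitment opens.

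**Illustration of exposure.** The article gives no control rate, alpha or power, so these figures rest on assumptions: exponential survival, hazard ratio 0.70 (the 30% reduction in the hypothesis), two-sided alpha 0.05 and control 2-year risk p. With λ = −ln(1 − p)/2 per year:

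- events = 250 × mean of [1 − exp(−λt)] + 250 × mean of [1 − exp(−0.7λt)], averaged over the follow-up times t
- power = Φ(√(events/4) × |ln 0.7| − 1.96)

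| Follow-up | Events, p = 20% to 60% | Events at p = 50% | Power at p = 50% | Events lost against two years |
|---|---|---|---|---|
| 24 months each | 86 to 268 | 221 | 0.76 | – |
| 18–22 months | 73 to 237 | 193 | 0.70 | 12–15% |
| 12–24 months | 66 to 218 | 176 | 0.66 | 19–23% |
| 10–22 months | 59 to 199 | 160 | 0.62 | 26–31% |

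**The case against.** **The death windows are upper limits.** A death within two years of randomization can be counted in a patient seen for 18 to 22 months, and Statistical methods plans Kaplan–Meier and Cox analyses, which handle administrative censoring. This stands. A reader might infer that the primary composite cannot be analysed; the documents do not support that.

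**No stated power is undermined.** A reader might also infer that the calendar leaves the trial underpowered or its event yield undefined. The article states no control rate, alpha or power, and their absence from a condensed article is no finding. The assumed risk also moves the event count more than the calendar does. The Operations Committee may increase the sample size after monitoring confirmed primary events, which partly offsets a shortfall. This stands too, so the event and power figures serve only as illustration.

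**The timetable may be the outlier.** The later sentence in Study development, the Follow-up period section and the two death definitions all point to two years. The patient-level rules may be right and the planning calendar wrong, in which case no 2-year data are lost. That is a fair reading, but the text does not choose it. It would also require moving the end of follow-up and the start of analysis. The contradiction remains whichever side is corrected.

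**An article condenses.** That excuses omissions. It does not excuse printed figures that conflict.

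**Conclusion.** The contradiction is real and needs correcting. The stated recruitment lengths (12 and 4 months) and follow-up figures (1.5-year average, two-year mean, two years for each patient) cannot all be true. With a close at month 24, mean follow-up is 16 to 20 months by reading. Nobody, or only patients randomized on day one, reaches the 2-year assessments.

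The follow-up ranges rest only on the printed dates; the means also assume uniform accrual. The two ways of stating a month-24 trial should not be merged: the listed calendar implies a mean of 20 months, while 1.5 years needs 12-month recruitment from month 0.

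What fails is the 2-year visit data, complete two-year observation for each patient, and a determinable closing date. The time-to-event analysis survives with censoring, and nothing firm can be said about power from this document.

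**What to change.** State one recruitment period and one closing rule, and use them in Study development, Follow-up period, Endpoint definitions, the DSMB text and Statistical methods. There are two consistent options.

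**(a) Keep two years for every patient**, as Follow-up period and Endpoint definitions say. Move the end of follow-up and the start of analysis to month 30 (recruitment in months 2–6), 36 (12 months from month 0) or 38 (12 months from month 2). The cost is 6, 12 or 14 more calendar months.

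**(b) Keep the common close at month 24.** Restate follow-up as the range and mean that the chosen recruitment period gives, count events from randomization to the close, and replace the 2-year visit with a close-out visit. This adds no calendar time, but it is more than a change of wording: the 2-year time point is given up and fewer events are observed than with two years for everyone.

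Under either option, correct the 1.5-year average and the two-year mean to match. Settle whether the interim described in Statistical methods and the 12-month review in the DSMB text are one look or two, and time the formal interim so that it falls before the close. Under (b) with 12-month recruitment, the present wording puts it at month 24 or 26.
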